#### Footnotes

- a Screening within 6 weeks of planned baseline visit. Prolongation of this period for legitimate reasons may be allowed upon written approval from the sponsor. Screening assessments can be done during the screening period and need not necessarily be done at the same moment. When the cap for enrolment has been reached for a specific IL28B genotype, stepwise screening can be performed, ie after signing of the ICF, IL28B screening can be done first. If the lab results show that the subject has another IL28B genotype than the one for which the enrolment cap was reached, further screening assessments can be undertaken.. Upon confirmation of all eligibility parameters, the baseline visit can take place.
- b The baseline visit should take place as soon as all details to confirm eligibility have been obtained.
- c Subjects who prematurely discontinue all study medication (TMC435/PegIFN $\alpha$ -2a/RBV) should switch to the visit schedule as laid out in Time and Events Schedule - Part 4 (unless the subject withdraws consent).
- d Including integrated consent for mandatory *IL28B* polymorphism analysis
- e Minimum criteria for the availability of documentation supporting the eligibility criteria are described in Section 17.4, Source Documentation.
- f Confirmation of liver disease status either by liver biopsy or non-invasive method as described in Section 4.1, Inclusion Criteria. If results are available from either a liver biopsy performed within 2 years prior to the screening visit or from non-invasive confirmation of the liver condition (by transient elastography) performed within 6 months prior to the screening visit, this assessment does not need to be repeated.
- g After the results have been obtained, all remaining blood samples for *IL28B* genotyping will be destroyed.
- h Only for subjects infected with genotype 4 HCV. If the schistosomiasis antibody test is positive, a schistosomiasis antigen blood test or rectal snip should be performed. Subjects with a positive schistosomiasis antigen blood test or positive rectal snip are excluded from study participation .
- i Alpha-fetoprotein (AFP) will be tested for all subjects. Follicle-stimulating hormone (FSH) will be tested for female subjects who are postmenopausal for less than 2 years.
- j Free thyroxine (T4) and free triiodothyronine (T3) will be assessed if TSH is abnormal.

- k Samples to be taken predose
- l The biochemistry sample at screening must be taken after the subject fasted for at least 12 hours. The biochemistry samples at baseline (Day 1) and Weeks 4 and 12 must be taken after fasting for at least 10 hours. It is recommended that biochemistry samples at all other time points also be taken after fasting for at least 10h. The homeostasis model assessment for insulin resistance (HOMA IR) index will be derived from insulin and glucose (fasted) test results at baseline and Weeks 4 and 12.
- m Urinalysis performed locally by dipstick. If there are clinically relevant abnormalities in the investigator's opinion, further urinalysis should be done locally (e.g., sediment analysis including RBC, WBC, casts). Clinically relevant findings from local urinalysis will be reported as AEs.
- n Including drug screen at central laboratory
- o Serum test at screening for all female subjects, urine test at other visits for women of childbearing potential. Pregnancy test should be performed prior to dosing.
- p See Time and Events Schedule - Part 3
- q Sequencing of the HCV NS3/4A region will be done in real-time for the baseline sample. Sequencing of the other samples will be at the discretion of the Study Responsible Scientist.
- r Including height and weight at screening. Physical examination at screening should include a fundoscopic eye examination, as per the manufacturer's prescribing information for PegIFN $\alpha$ -2a. Note: Baseline fundoscopic pathology which would require routine follow up on PegIFN $\alpha$ -2a and RBV therapy is considered exclusionary, as per exclusion criterion 7.
- s PRO scales should be completed prior to any other study-related activity at each visit.
- t From signing the Informed Consent Form (ICF) until 4 weeks after last study medication intake. Thereafter, only AEs considered related to TMC435 will be reported. SAEs will be reported until 30 days after last study-related procedure.

## TIME AND EVENTS SCHEDULE - PART 2: FROM WEEK 12 TO WEEK 36 FOR SUBJECTS ELIGIBLE FOR A TOTAL TREATMENT DURATION OF 12 WEEKS

| Period                                                                                               | Study Visits |    |     |     |
|------------------------------------------------------------------------------------------------------|--------------|----|-----|-----|
| Visit Number                                                                                         | V8           | V9 | V10 | V11 |
| Study Week                                                                                           | 16           | 20 | 24  | 36  |
| Study Procedure                                                                               |              |    |     |     |
| Clinical Laboratory Tests                                                                     |              |    |     |     |
| TSH a                                                                                     |              |    | X   | X   |
| Hematology/biochemistry b                                                                 | X            | X  | X   | X   |
| Local urinalysis c                                                                        | X            | X  | X   | X   |
| Pregnancy test d                                                                          | X            | X  | X   | X   |
| Efficacy Assessments                                                                          |              |    |     |     |
| HCV RNA quantification                                                                               | X            | X  | X   | X   |
| Viral sequencing c                                                                        | X            | X  | X   | X   |
| Liver disease status f                                                                    |              |    |     | X   |
| Other Safety Assessments                                                                      |              |    |     |     |
| Physical examination                                                                                 | X            | X  | X   | X   |
| Vital signs                                                                                          | X            | X  | X   | X   |
| Patient reported outcomes (PRO)                                                               |              |    |     |     |
| Hepatitis C Symptom & Impact Questionnaire (HCV-SIQ) g                                    | X            | X  | X   | X   |
| Fatigue (Fatigue severity scale [FSS]) g                                                  | X            |    | X   | X   |
| Productivity (Work Productivity and Activity Impairment [WPAI]) g                         | X            |    | X   | X   |
| Depressive symptom severity (Center for Epidemiologic Studies Depression Scale [CES-D]) g | X            |    | X   | X   |
| Health status (EuroQol 5-dimension questionnaire [EQ-5D]) g                               | X            |    | X   | X   |
| Ongoing Subject Review                                                                        |              |    |     |     |
| Concomitant therapy                                                                                  | X            | X  | X   | X   |
| Observe/interview for (serious) adverse events h                                          | X            | X  | X   | X   |

### Footnotes

a Free thyroxine (T4) and free triiodothyronine (T3) will be assessed if TSH is abnormal.

b The biochemistry sample at Weeks 24 and 36 must be taken after fasting for at least 10 hours. It is recommended that biochemistry samples at all other time points also be taken after fasting for at least 10h. The homeostasis model assessment for insulin resistance (HOMA IR) index will be derived from insulin and glucose (fasted) test results at Weeks 24 and 36.

c Urinalysis performed locally by dipstick. If there are clinically relevant abnormalities in the investigator's opinion, further urinalysis should be done locally (e.g., sediment analysis including RBC, WBC, casts). Clinically relevant findings from local urinalysis will be reported as AEs.

d Urine test for women of childbearing potential. Extra pregnancy test kits will be given if more than 4 weeks between two consecutive study visits to perform a pregnancy test at home.

- e Sequencing of the HCV NS3/4A region will be done at the discretion of the Study Responsible Scientist.
- f Non-invasive confirmation of the liver condition (by transient elastography). All effort should be made to use the same assessment method as used to assess fibrosis stage at inclusion.
- g PRO scales should be completed prior to any other study-related activity at each visit.
- h From signing the Informed Consent Form (ICF) until 4 weeks after last study medication intake. Thereafter, only AEs considered related to TMC435 will be reported. SAEs will be reported until 30 days after last study-related procedure.

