#### Footnotes

a Subjects who prematurely discontinue all study medication (PegIFN $\alpha$ -2a/RBV) should switch to the visit schedule as laid out in Time and Events Schedule - Part 4 (unless the subject withdraws consent).

b Free thyroxine (T4) and free triiodothyronine (T3) will be assessed if TSH is abnormal.

- c The biochemistry sample at Weeks 24, 36, and 48 must be taken after fasting for at least 10 hours. It is recommended that biochemistry samples at all other time points also be taken after fasting for at least 10h. The homeostasis model assessment for insulin resistance (HOMA IR) index will be derived from insulin and glucose (fasted) test results at Weeks 24, 36, and 48.
- d Urinalysis performed locally by dipstick. If there are clinically relevant abnormalities in the investigator's opinion, further urinalysis should be done locally (e.g., sediment analysis including RBC, WBC, casts). Clinically relevant findings from local urinalysis will be reported as AEs.
- e Urine test for women of childbearing potential. Extra pregnancy test kits will be given if more than 4 weeks between two consecutive study visits to perform a pregnancy test at home.
- f Sequencing of the HCV NS3/4A region will be done at the discretion of the Study Responsible Scientist.
- g Non-invasive confirmation of the liver condition (by transient elastography). All effort should be made to use the same assessment method as used to assess fibrosis stage at inclusion.
- h PRO scales should be completed prior to any other study-related activity at each visit.
- i From signing the ICF until 4 weeks after last study medication intake. Thereafter, only AEs considered related to TMC435 will be reported. SAEs will be reported until 30 days after last study-related procedure.

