##### **4.1. Inclusion Criteria**

Each potential subject must satisfy all of the following criteria to be enrolled in the study. Exceptional and limited retesting of abnormal screening values that lead to exclusion is allowed only once using an unscheduled visit during the screening period (to reassess eligibility). This should only be considered if there is no anticipated impact on subject safety. Refer to Section 9.1.2 for full details.

1. Subject must be a man or woman 18 to 70 years of age, inclusive, prior to the baseline visit.
2. Subject must have confirmed chronic HCV infection as documented by a positive anti-HCV antibody test, or positive HCV RNA test at least 6 months prior to screening, or positive HCV genotyping test at least 6 months prior to screening.

3. Subject's liver disease stage must be equivalent to Metavir Score F0-F2 (no fibrosis, or portal fibrosis without or with few septa) as confirmed by a liver biopsy performed within 2 years prior to screening or by non-invasive determination of liver disease stage (by transient elastography) performed within 6 months prior to screening. Non-invasive staging assessments include FibroScan™ or MR-Elastography.

Note: The Metavir scoring system is provided in Attachment 1. For non-invasive fibrosis assessment, FibroScan™ should be < 8 kPa and MR-Elastography should be < 3.1 kPa. For any other transient elastography method (eg, Shear Wave Elastography), please contact the sponsor for advice.

4. Subject with liver disease stage equivalent to Metavir Score F2 and without liver biopsy performed within 2 years prior to screening must have undergone liver imaging (ultrasound, computed tomography [CT], or magnetic resonance imaging [MRI]) within 6 months prior to the Screening visit (or between the Screening and Baseline/Day 1 visits) with no findings suspicious of hepatocellular carcinoma.
5. Subject must have genotype 1 or genotype 4 HCV infection (confirmed at screening).
6. Subject's plasma HCV RNA must be > 10000 IU/mL at screening.

Note: Retesting of HCV RNA to assess eligibility will be allowed once, using an unscheduled visit during the screening period.

7. Subject has not received prior treatment for hepatitis C with any approved or investigational drug.
8. Before screening, a woman must be either:

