### Other Secondary Endpoints

In subjects with genotype 1 or genotype 4 HCV infection for both genotypes combined (subanalyses for each genotype separately will also be done):

- Mean change from baseline at each study visit specified in the Time and Events Schedule throughout treatment and follow-up for each of the following PRO measures:
  - HCV-SIQ symptom score
  - HCV impact score
  - FSS total score
  - CES-D score
  - WPAI missed work time
  - WPAI daily activity impairment
  - WPAI productivity score
  - EQ5D VAS
  - EQ5D valuation index
  - EQ5D Descriptive System scores

In subjects with genotype 1 or genotype 4 HCV infection (separately per genotype):

- the proportion of subjects with normalized ALT levels at the end of study and at time points SVR is assessed.
- Change in liver disease stage assessment between screening assessment and assessment at SVR24 time point

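### For subjects staged by biopsy at entry, change in liver disease stage compares histology with elastography, and the same-method instruction cannot be met

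*Protocol*

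**What the plan says.** **Endpoint.** Protocol Section 9.2.2, Other Secondary Endpoints, lists per genotype: "Change in liver disease stage assessment between screening assessment and assessment at SVR24 time point". The Synopsis (Efficacy) lists it as well.

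**Entry.** Section 4.1, inclusion criterion 3, sets the range: "Subject's liver disease stage must be equivalent to Metavir Score F0-F2". The stage may be established "as confirmed by a liver biopsy performed within 2 years prior to screening or by non-invasive determination of liver disease stage (by transient elastography", the latter within 6 months of screening. The criterion continues: "Non-invasive staging assessments include FibroScan™ or MR-Elastography". Its note gives a limit for each device, "FibroScan™ should be < 8 kPa and MR-Elastography should be < 3.1 kPa", and adds: "For any other transient elastography method (eg, Shear Wave Elastography), please contact the sponsor for advice". Footnote f of Time and Events Schedule Part 1 says that an in-window result, biopsy or non-invasive, is not repeated.

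**Follow-up.** Liver disease status is scheduled once more, at Week 36 (Part 2, footnote f) or Week 48 (Part 3, footnote g). Both footnotes say: "Non-invasive confirmation of the liver condition (by transient elastography). All effort should be made to use the same assessment method", meaning the method that established the fibrosis stage at inclusion. Biopsy is not offered at this visit.

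**The concern.** The endpoint is meant to describe what happens to liver disease stage between entry and 24 weeks after planned end of treatment. That requires the two readings to be on the same footing. For a subject who entered on a biopsy they are not: the first is a histological stage that may be 2 years old at screening, and the second is an elastography result. The footnotes ask for the same method while excluding the only method that would be the same.

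An observed change in such a subject may reflect the switch of method, disease change before the first dose, or change after it. These cannot be separated afterwards, because the protocol requires no elastography at baseline from a subject who has an eligible biopsy. Pooling these subjects with those measured by one method throughout gives a summary with no clear meaning.

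**Working it through.** No sample size, power or effect size is stated for this endpoint, so there is no figure to reproduce. The check sets the methods side by side, then looks at the intervals, then at selection.

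**1. Can both footnote sentences be met?**

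| Staged at entry by | Elastography at SVR24 | Same method as entry | Both |
|---|---|---|---|
| Biopsy | prescribed | impossible | no |
| FibroScan | prescribed | possible | yes |
| MR-Elastography | prescribed; criterion 3 groups it with the accepted non-invasive methods | possible | yes |

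For the last two rows the instruction is one of best effort, so a cross-method pair remains possible. The protocol does not say how such a pair is handled.

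**2. What the change contains for a biopsied subject.** Let H be the histological stage the subject would show at a given time, and E the stage read from elastography. Then

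E(SVR24) − H(biopsy) = [E(SVR24) − H(SVR24)] + [H(SVR24) − H(Day 1)] + [H(Day 1) − H(biopsy)].

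The first bracket is method difference, the second is change since treatment began, and the third is change before treatment. Only the second is of interest. If a share p of subjects entered on biopsy, the pooled mean carries p times the average of the first and third brackets. The protocol does not give p or either average, so p can be anything from 0 to 1.

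**3. Intervals.** Inputs: biopsy up to 2 years (104 weeks) or non-invasive staging up to 6 months (taken as 26 weeks) before screening (Section 4.1); screening up to 6 weeks (Section 9.1.2); SVR24 visit at Week 36 or 48 (Schedule Parts 2 and 3).

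| Entry method | Before Day 1 | To Week 36 | To Week 48 |
|---|---|---|---|
| Biopsy | 104 + 6 = 110 | 110 + 36 = 146 (about 2.8 years) | 110 + 48 = 158 (about 3.0 years) |
| Non-invasive | 26 + 6 = 32 | 32 + 36 = 68 | 32 + 48 = 80 |

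At the limit, 110/146 = 75% of a biopsied subject's interval on the Week 36 schedule precedes treatment, against 32/68 = 47% for a subject staged non-invasively. Screening may be prolonged with sponsor approval, so these are not absolute maxima.

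**4. Selection below an entry ceiling.** Subjects staged non-invasively enter only if the reading is under the limit for the device. With no true change, entry value X₁, follow-up value X₂, mean μ and test-retest reliability ρ on the log scale, E[X₂ − X₁ | X₁ < c] = (1 − ρ)(μ − E[X₁ | X₁ < c]), which is positive. Sizes need figures the protocol does not give. **Assumed**: log-normal FibroScan values, median 5.5 to 7.5 kPa, log-SD 0.35, reliability 0.70 to 0.95, 1,000,000 draws per setting, selection at < 8 kPa.

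| Setting (no true change) | ≥ 8 kPa at follow-up | Mean change | Share falling |
|---|---|---|---|
| Median 5.5, reliability 0.95 | 3.3% | +0.04 kPa | 48% |
| Median 7.5, reliability 0.70 | 21.7% | +0.58 kPa | 39% |

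These two settings are the extremes of the grid. The drift favours apparent worsening, yet many subjects still show a fall. It arises even when one method is used throughout.

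**The case against.** The best defence is that the plan anticipates the problem: both footnotes ask for the inclusion method to be used again, so within-method comparison is the intention. The endpoint is descriptive and ranks as other secondary; the only test specified, in Section 11.3, concerns SVR12 in genotype 1. Few subjects may have entered on biopsy. Section 11 leaves details to the Statistical Analysis Plan, which is not shown and could restrict the comparison.

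Most of this stands and limits the weight of the point. It does not remove it. The same-method sentence cannot help biopsied subjects, and an analysis plan cannot supply a baseline elastography value that was never required or repair conflicting wording in a site schedule.

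A reader might infer more than the protocol supports:

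- *That MR-Elastography subjects are switched to FibroScan.* Criterion 3 lists MR-Elastography among the accepted non-invasive methods and calls shear wave another transient elastography method. In the protocol's usage, repeating MR-Elastography meets both footnote sentences.
- *That everyone was selected under one cut-off.* There are two device limits and, for biopsied subjects, a Metavir criterion.
- *That the endpoint cannot show improvement.* Entry covers F0 to F2 on a 0-to-4 scale, so F1 can fall by one stage and F2 by two; only F0 can do nothing but rise. One-directional change would follow only if the eligibility limits were also the scoring rule. Nothing says so, and criterion 4 presupposes that F2 can be recognised without a biopsy.
- *That the ratio of the two limits, 8/3.1 or about 2.6, measures the bias.* The endpoint is change in stage, not in kPa, so that ratio says nothing about its size.

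**Conclusion.** The point holds for subjects staged by biopsy at entry. For them the two footnote sentences conflict, and the change in stage mixes method difference and up to 110 weeks of pre-treatment change with change since treatment began, over at most about 146 weeks (Week 36 schedule) or 158 weeks (Week 48 schedule) with a 6-week screening phase. This follows from the protocol text alone. The effect on the pooled result cannot be sized, because neither the share staged by biopsy nor the average method difference is given.

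For subjects staged non-invasively the instruction can be met; the remaining weakness is that best effort admits cross-method pairs without a rule for them. Regression to the mean from the entry ceilings is a separate caution for interpretation, and its sizes above rest entirely on assumed distributions. The consequence is confined to one descriptive endpoint. Eligibility, treatment duration and the primary conclusion are untouched. The correction is worth making because following the current text produces an uninterpretable comparison.

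**What to change.** 1. In Section 9.2.2 and the Synopsis, define the endpoint as change in liver disease stage among subjects assessed by the same non-invasive method at screening and at the SVR24 visit.
2. Report biopsy-entry subjects and cross-method pairs separately, giving the entry and SVR24 results without a change score.
3. Reword footnote f of Part 2 and footnote g of Part 3 along these lines: *using the same non-invasive method as at inclusion; subjects staged by biopsy at entry are not included in the change analysis*.
4. State with the result that selection below the entry ceilings favours apparent worsening through regression to the mean. The change above does not remove this. It also leaves up to 32 weeks of pre-treatment time in the interval for subjects staged non-invasively.

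The cost is wording only, with no added procedure. Fewer subjects contribute to the change summary; how many fewer depends on the share staged by biopsy, which should be reported.

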### TIME AND EVENTS SCHEDULE - PART 3: FROM WEEK 12 TO WEEK 48 FOR SUBJECTS ELIGIBLE FOR A TOTAL TREATMENT DURATION OF 24 WEEKS (EXTENSION)

| Period                                                                                               | Study Visits a |    |     |     |     |     |
|------------------------------------------------------------------------------------------------------|---------------------------|----|-----|-----|-----|-----|
| Visit Number                                                                                         | V8                        | V9 | V10 | V11 | V12 | V13 |
| Study Week                                                                                           | 16                        | 20 | 24  | 28  | 36  | 48  |
| Study Procedure                                                                               |                           |    |     |     |     |     |
| Clinical Laboratory Tests                                                                     |                           |    |     |     |     |     |
| TSH b                                                                                     |                           |    | X   |     | X   | X   |
| Hematology/biochemistry c                                                                 | X                         | X  | X   | X   | X   | X   |
| Local urinalysis d                                                                        | X                         | X  | X   | X   | X   | X   |
| Pregnancy test e                                                                          | X                         | X  | X   | X   | X   | X   |
| Study Drug Administration                                                                     |                           |    |     |     |     |     |
| Dispense PegIFN $\alpha$ -2a/RBV: Extension                                                          | X                         | X  |     |     |     |     |
| Efficacy Assessments                                                                          |                           |    |     |     |     |     |
| HCV RNA quantification                                                                               | X                         | X  | X   | X   | X   | X   |
| Viral sequencing f                                                                        | X                         | X  | X   | X   | X   | X   |
| Liver disease status g                                                                    |                           |    |     |     |     | X   |
| Other Safety Assessments                                                                      |                           |    |     |     |     |     |
| Physical examination                                                                                 | X                         | X  | X   | X   | X   | X   |
| Vital signs                                                                                          | X                         | X  | X   | X   | X   | X   |
| Patient reported outcomes (PRO)                                                               |                           |    | X   |     |     |     |
| Hepatitis C Symptom & Impact Questionnaire (HCV-SIQ) h                                    | X                         | X  | X   | X   | X   | X   |
| Fatigue (Fatigue severity scale [FSS]) h                                                  | X                         | X  | X   |     | X   | X   |
| Productivity (Work Productivity and Activity Impairment [WPAI]) h                         | X                         | X  | X   |     | X   | X   |
| Depressive symptom severity (Center for Epidemiologic Studies Depression Scale [CES-D]) h | X                         | X  | X   |     | X   | X   |
| Health status (EuroQol 5-dimension questionnaire [EQ-5D]) h                               | X                         | X  | X   |     | X   | X   |
| Ongoing Subject Review                                                                        |                           |    |     |     |     |     |
| Concomitant therapy                                                                                  | X                         | X  | X   | X   | X   | X   |
| Observe/interview for (serious) adverse events i                                          | X                         | X  | X   | X   | X   | X   |

